### Participants

Up to 200 older adults (65–84 years of age) with mild to moderately severe sensorineural hearing loss^1^ are recruited from October 2024 onwards at the KUH among patients referred to the ENT clinic for HA rehabilitation of sensorineural hearing loss. Patients with conductive or asymmetrical hearing loss, HA contraindications, diagnosed cognitive impairment or cognitive concern under evaluation or any health condition affecting their ability to participate in the study are excluded. The eligibility criteria for the trial are presented in table 1. Patients are first screened as part of their routine hearing loss assessment appointment by an ENT specialist, and eligible patients are invited to participate in the study. A study nurse will obtain informed consent from the participants during the same appointment (online supplemental material S2). The recruitment for this study started on 1 October 2024, and the anticipated primary completion date is estimated to be 29 February 2028.

**Table 1 T1:** Eligibility criteria

Inclusion criteria	Exclusion criteria
Age 65–84 years	Conductive hearing impairment (air-bone gap>20 dB HL in two consecutive frequencies)
Mild to moderately severe sensorineural hearing loss, pure-tone average (0.5–4 kHz) between 20 and 64 dB*	Difference between the hearing levels of the ears is >15 dB HL in three consecutive frequencies
Community-dwelling, that is, living at home/not living in a care home or nursing home	HA contraindication
Proficiency in Finnish language	Cognitive status: Previously diagnosed dementia or current use of cholinesterase inhibitors and/or memantine. If there is a current ongoing diagnostic process for suspected dementia, the decision on eligibility will be made by an experienced study physician based on medical records and clinical judgement.
First-time HA user	Any health conditions severely impairing vision (no predefined visual acuity threshold), mobility, communication or ability to participate in study visits and complete study assessments, as judged by the study nurse and/or physician.

* As per the Global Burden of Disease Expert Group on hearing loss criteria.

dB HL, decibel hearing level; HA, hearing aid.

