#### Secondary outcomes

Changes in the following secondary endpoints will be included: Hearing in Real-Life Environment (HERE)^22^ and Speech, Spatial and Qualities of Hearing Scale (SSQ)^23^; HA usage, self-report and HAs log-data; listening effort questionnaire^24^; response time of the DIN test and tinnitus handicap inventory (THI)^25^; Consortium to Establish a Registry for Alzheimer’s Disease -test’s (CERAD-nb) global and domain scores^26^; Clinical Dementia Rating Sum of Boxes^27^; health-related quality of life (15D and EQ5-D-5L questionnaires^28
29^); self-reported depression symptoms and Beck Depression Inventory^30^ (table 2, online supplemental materials S3 and S4).

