### Study intervention

Participants in the DDHR intervention group will receive data-driven and regularly controlled HA rehabilitation that is not part of the standard care protocol. Prescription HAs with custom earmoulds will be fitted by using REM in accordance with the recommendations of the latest ISO standard (21388:2020) and a recent review article on the best practices for HA fitting.^33^ In addition, preliminary unpublished findings from the benefits of REM (BREM) study (ClinicalTrials.gov identifier: NCT05621798) suggest that REM-based fitting may result in improved SPIN performance compared with conventional fitting methods. The fittings are conducted by audiometricians specifically trained in the DDHR programme procedures. The gain of sound amplification is set to 100%. After the fitting of the HAs, participants’ auditory-related outcomes will be assessed at the 3-, 6- and 12-month follow-up visits using the DIN test. If needed, re-fitting will be performed based on the following criteria derived from the preliminary data of the BREM study:

The absolute improvement in the DIN<1.5 dB (SNR), ORThe absolute result of the DIN test>than −8.5 dB (SNR), ORThe participant is unsatisfied with the HA fitting.

If re-fitting is needed, the log-data of the HAs will be verified, and the following procedures will be performed based on the audiometrician’s clinical experience:

Overall usage <6 hour/day: The reason for low usage is probed, and the participant is encouraged to use the HA more. If the amplification of the HA is reported to be too loud, the sound amplification gain can be lowered to 90%. Fine-tuning of specific frequencies is also allowed based on the participants’ feedback.Overall usage ≥6 hour/day: The participant’s satisfaction with ongoing HA rehabilitation is inquired. If the participant is satisfied, no further adjustments are needed. If the participant is unsatisfied, the audiometrician is allowed to change the sound amplification gain between 90% and 110% or perform fine-tuning of specific frequencies depending on the participant’s feedback.

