### Control group

The participants in the control group will receive standard care HA rehabilitation currently conducted at the KUH ENT clinic. Prescription HAs with custom earmoulds will be fitted using the manufacturers’ proprietary fitting algorithms and REM fitting will be performed only in complex cases, based on the clinical judgement of the audiometrician. In the control group, HA fittings are performed by audiometricians following routine clinical practice and who have not received specific training in the HAHA study procedures. Three months after the HA fitting, participants will be contacted via telephone and asked about the status of the rehabilitation. Additional monitoring visits may be offered based on participant feedback. Individual HA settings will be decided by the audiometrician based on clinical judgement and without predefined sound amplification gain levels. Further adjustments will be made only on a participant’s request. Due to the possible variability of the fitting procedures, the key rehabilitation process variables will be documented (eg, fitting verification method, number of follow-ups, types of adjustments and HA usage data) and reported descriptively.

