Change in HERE, SSQ, listening effort questionnaire, response time and THI will be analysed as a function of randomisation group, time (continuous in days from baseline) and group×time interaction. Data from baseline and 12-month visits will be used to analyse short-term intervention effects, and data from baseline, 12- and 24-month visits will be used for longer-term effects.Change in HA usage will be analysed as a function of randomisation group, time (continuous in days from primary HA fitting) and group×time interaction. Data from the 3- and 12 month visits will be used to analyse short-term intervention effects, and data from the 3-, 12- and 24-month visits will be used for longer-term effects.

Analyses of cognitive outcomes, where a longer time is needed to observe significant change compared with auditory outcomes, will focus mainly on the longer-term effects, analysed based on data from baseline and 12- and 24-month visits.

Analyses of quality of life and other psychosocial outcome measures will include both short-term (baseline and 12months) and longer-term (baseline, 12- and 24 months) intervention effects. Additional information on sensitivity analyses, accounting for missing or spurious data, and reporting dropouts is presented in online supplemental material S5.

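### Hearing-aid usage is modelled as group×time from 3 months after fitting, so the interaction measures later drift rather than the usage benefit, and the 3-month value is not secured alike in both arms

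*Protocol article*

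**What the plan says.** The Secondary outcomes section of the Protocol article gives usage two sources: "HA usage, self-report and HAs log-data". The Statistics section sets the model: "Change in HA usage will be analysed as a function of randomisation group, time (continuous in days from primary HA fitting) and group×time interaction". It then sets the data: "Data from the 3- and 12 month visits will be used to analyse short-term intervention effects", with the 24-month data added for longer-term effects. The other auditory outcomes in that section use the same kind of model but start from the baseline visit.

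Four other places bear on this:

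- Table 1 (Participants) requires each participant to be a "First-time HA user".
- Control group: "Three months after the HA fitting, participants will be contacted via telephone and asked about the status of the rehabilitation". Beyond that, "Additional monitoring visits may be offered based on participant feedback". The Discussion likewise describes outcome monitoring of controls as telephone only.
- Table 2 (Data collection) shows a telephone call for standard care at 3 months and marks outcome variables at baseline, 12 and 24 months.
- Study intervention gives the DDHR arm visits at 3, 6 and 12 months and describes one log-reading step: "If re-fitting is needed, the log-data of the HAs will be verified".

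**The concern.** For an outcome measured before randomisation, group×time carries the treatment effect because the arms start level. Usage has no such starting point. Before fitting it is zero by design, and by 3 months each participant has worn aids fitted by the method of the allocated arm. A gain achieved by then sits in the starting value, and the interaction does not count it. The plan nevertheless presents this model as the analysis of short-term intervention effects and names no other contrast.

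The Statistics section also relies on a 3-month visit that controls are not scheduled to have. If the 3-month value is a device log in one arm and a telephone answer in the other, or is missing more often in one arm, the interaction mixes drift with a difference in measurement.

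At stake is the reading of an outcome close to the programme's rationale: the Study design section links the lack of systematic outcome assessment in routine care to reduced adherence to hearing-aid use.

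**Working it through.** **The plan's own figure.** None is given for usage. The only computed figure is the sample size for the speech-in-noise comparison, and it reproduces. With a difference of 1.1 dB (−0.9 against −2), SDs of 1.2 and 2.5, and two-sided alpha 0.025 (sidedness assumed), a Welch test with 81 per arm has power 0.901, and 81/0.90 = 90 per arm. I use 81 per arm below.

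**What each term estimates.** Let T and C be mean usage in the DDHR and control arms, with the subscript giving the month.

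- Interaction over the interval = (T12 − T3) − (C12 − C3).
- Effect on usage at 12 months = T12 − C12.

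Illustration in assumed h/day:

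- DDHR 8→8, control 6→6: the 12-month effect is 8 − 6 = +2; the interaction is 0 − 0 = 0.
- DDHR 8→8, control 5→6: the 12-month effect is +2; the interaction is 0 − 1 = −1.

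The group coefficient alone is not the 12-month contrast either. With time counted from fitting, it is the difference extrapolated to day 0. If the difference is 2 at day 91 and 1 at day 365, the slope is −1/274 per day and the day-0 value is 2 + 91/274 = 2.33, while the 12-month difference is 1. The 12-month contrast is the group coefficient plus 365 times the interaction coefficient.

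**Size.** Assumptions, none from the documents: SD 4 h/day, within-person correlation 0.4/0.6/0.8, two-sided 5% tests, 4,000 simulated trials per cell.

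| Difference at 3 → 12 months (h/day) | Interaction rejects | 12-month comparison rejects |
|---|---|---|
| 2 → 2 | 5% / 5% / 5% | 89% / 88% / 88% |
| 2 → 1 | 31% / 42% / 71%, pointing against DDHR | 35% / 36% / 35% |
| 0 → 2 | 82% / 94% / over 99% | 89% / 88% / 89% |

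Hand check of the first row: SE = 4·√(2/81) = 0.629, 2/0.629 = 3.18, and power ≈ Φ(3.18 − 1.96) = 0.89. Hand check of the second row at correlation 0.6: SD of change = 4·√(2·0.4) = 3.58, SE = 3.58·√(2/81) = 0.562, and power ≈ Φ(1/0.562 − 1.96) = Φ(−0.18) = 0.43.

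**If controls have no 3-month value.** Time is in years and the residual SD is 1, with observations treated as independent.

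- Both arms at days 91 and 365: the sum of squares of time per arm is 162·(0.751/2)² = 22.8, so the SE of the interaction is √(2/22.8) = 0.30. The design has full rank (4 of 4).
- Controls at exactly 12 months only: rank 3 of 4, so the interaction is not estimable.
- Controls at 12 months with an assumed 14-day SD in visit dates: the sum of squares is 81·(14/365)² = 0.119, so the SE is √(1/0.119 + 1/22.8) ≈ 2.9 (3.1 in one simulated draw). That is about ten times larger and rests only on scatter in visit dates.

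In the longer-term model the control slope would come from 12 to 24 months and the DDHR slope from 3 to 24 months, which are different windows.

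**The case against.** The strongest reply is that the model can be run and can give the right answer. Usage has a self-report source, controls are telephoned at 3 months, and the Control group section says usage data will be documented for them. With 3- and 12-month values in both arms the model is fully identified. It contains a group term, the article does not say which coefficient is tested, and a 12-month difference can be drawn from the fit. The analysis plan, which is not shown, may name that contrast. This stands against any claim that the analysis cannot be carried out. It does not remove the mismatch: the outcome is stated as change, the first value is post-treatment, and the contrast that would answer the question is not named.

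Table 2 is also weaker evidence than it looks. Its outcome row has no mark at 3 or 6 months, yet the DDHR arm has the digits-in-noise test at both, so the row does not list every measurement. Supplement S3 is not shown and may schedule usage at 3 months.

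A reader might infer that DDHR logs are read only in poorer responders. The text does not say so. It describes log verification as a step of the re-fitting procedure, not as the way outcome data are captured, and log-data are listed as an outcome for the trial. Nor can such a subset be sized from the planning assumption. Φ((1.5 − 2)/2.5) = 0.42 applies a 12-month figure to a 3-month reading and covers one of three criteria joined by OR.

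Finally, the interaction is not useless. If the benefit emerges only after 3 months it performs well, as the third row of the table shows.

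**Conclusion.** The point holds for a secondary outcome. As written, group×time measures differential change after 3 months. It is blind to a benefit already constant by then (about 5% rejection against 88–89%), and it can point against DDHR when a real benefit narrows. These percentages rest on the assumed SD, correlations and effects. That a constant benefit gives an interaction of zero needs no assumption.

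The Statistics section also conflicts with the Control group section and Table 2 on whether controls have a 3-month visit. The consequence is conditional: 3-month usage may differ between arms in mode and completeness, and the short-term interaction for log-data is practically not estimable if controls have no 3-month reading. Self-reported usage could still be modelled.

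It would go too far to conclude that a usage benefit will be reported as absent or as harm. That depends on which coefficient is reported, and the article leaves this open. The primary outcomes, their multiplicity adjustment and the sample size are not affected.

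**What to change.** 1. Define the usage effect as the between-arm difference in mean daily usage at 12 months and, separately, at 24 months. Measure it the same way in both arms at the outcome visits both attend, and report this contrast instead of group×time as the intervention effect.
2. State for each source, self-report and device log, when and how it is captured in each arm.
3. Use 3-month usage descriptively, or in the model only if the same method captures it in both arms.
4. Reconcile the usage paragraph in Statistics with Table 2 and the Control group section on the 3-month contact.

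The cost is wording in the protocol or analysis plan, best settled before any comparison by arm is seen. The 12- and 24-month readings fall at visits already scheduled for both arms. The small loss is that differential change from 3 to 12 months becomes a supportive analysis.

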### Ethics and dissemination

#### Ethics approval and consent to participate

This study is conducted in accordance with the Declaration of Helsinki and the International Conference on Harmonisation for Good Clinical Practice (ICH GCP E6). The study protocol and relevant documents were approved by the Regional Medical Research Ethics Committee of the well-being Services County of North Savo (approval no. 697/2023). Informed consent is obtained from each participant before initiating the study-specific procedure. This trial has been registered at ClinicalTrials.gov (NCT06495268, first release 2 July 2024). The version number of the protocol document at the time of submission of this article was 2.1 (date: 11 November 2024).

The Trial Steering and Management Group (TSMG), comprising the co-principal investigators, senior investigators and relevant study staff, will oversee trial conduct and progress and meet at least monthly throughout the study. An independent Data and Safety Monitoring Board of 3–4 experts in clinical trials, research and statistics will review safety data and advise the TSMG. The co-PIs will oversee data quality and integrity, and the trial site (KUH) will be periodically monitored by representatives of the University of Eastern Finland Brain Research Unit.

Trained HAHA personnel will enter case report form data into the database. All entries will be approved by the primary investigator or designee, and all post-submission changes will be electronically audit-trailed and dated.

#### Availability of data and materials

The full protocol will be published with the main trial results. Trial data and samples will remain confidential until analysis and review are complete and may not be published without TSMG approval. Data and samples will be available for collaborative research after publication of the main results on TSMG-approved application. Findings will be disseminated through peer-reviewed publications, conference abstracts and other standard channels.

## Discussion

The primary scope of the HAHA study, as a proof-of-concept trial, is to test a novel precision medicine model for hearing rehabilitation by approaching hearing loss as a broader degenerative entity with multifaceted manifestations that are currently unaddressed in clinical practice. Our goal is to determine whether a structured, data-driven rehabilitation approach that optimises functional hearing performance leads to measurable differences in communication ability and whether these improvements are associated with neural or cognitive correlates assessed through secondary outcomes (eg, imaging and electrophysiological measures). Additionally, a key objective is methodological: to identify sensitive and feasible outcome measures for assessing long-term HA benefits that could be used in a full-scale RCT and for effective hearing rehabilitation in the future.

Despite the negative consequences of hearing loss and the benefits of HAs, their uptake remains relatively low, even in countries where they are provided free of charge.^35
36^ Additionally, a significant proportion of those who have prescribed HAs do not use them, with no or irregular use up to 80%.^37^ There is a lack of consensus on which outcomes are relevant for the reliable quantification of HA benefits or which are important for maintaining brain health.^38^ Cochrane reviews on hearing rehabilitation^6
39^ recommend that future research address evidence gaps by focusing on long-term outcomes (≥1 year), developing standardised outcome measures and designing studies that capture benefits beyond HA provision. The HAHA trial aims to address these recommendations by identifying and providing currently missing relevant outcomes for an accurate assessment of the effectiveness of hearing rehabilitation. Additionally, the trial seeks to establish an evidence-based approach to examine hearing loss as a broader degenerative condition, integrating aspects beyond just providing HAs. These aspects include optimised hearing rehabilitation, the association between cognitive decline and hearing loss, the impact of DSI on hearing rehabilitation outcomes and the effect of hearing loss on quality of life and other psychosocial outcomes. Eventually, the results of this study may inform future best practice guidelines for hearing rehabilitation.

More specifically, this trial aims to provide new evidence on auditory processing and neural mechanisms of hearing rehabilitation and its impact on cognition, as well as identify novel, accessible and non-invasive biomarkers predicting hearing rehabilitation benefits on cognitive decline (eg, EEG-derived CAEPs as predictors of hearing rehabilitation benefit; SPIN and retinal imaging biomarkers for cognitive decline).

The HAHA trial is based on a novel pragmatic approach that is fully embedded in routine specialised care. Hearing rehabilitation in Finland is centralised to the specialised hearing centres of district/university hospitals, where patients with hearing loss are referred from primary care. Specialised hearing centres follow a standard clinical protocol for hearing loss assessment and rehabilitation, and the costs of HAs are reimbursed by the well-being Services counties. At present, the standard clinical protocol in Finland includes only the fitting of HAs at the audiometrician’s appointment, and further appointments are arranged based only on patient feedback. The HA fitting method used is generally the initial fit, regardless of the recommendations to use REM-based fitting. Although the DDHR approach in this trial is designed to optimise functional hearing outcomes, its structured procedures may require additional clinical resources that are not necessarily available in routine audiology practice. Therefore, assessing feasibility and identifying scalable implementation strategies are important secondary objectives of this proof-of-concept study.

In the HAHA study, all trial participants will be fitted according to the standard care protocol for the control group and using the novel DDHR programme for the intervention group. The main difference between these rehabilitation groups is that the outcomes of the HA rehabilitation are verified for the intervention group, while the control group only receives the HAs, and the monitoring of the outcomes is done only via a phone call. The HAs provided for the study groups are the same as in the Finnish standard clinical protocol, but the HA fitting method used for the intervention group is REM-based fitting. This unique rehabilitation approach of the intervention group, with proper fitting and outcome verification, will be crucial to optimise the current hearing loss clinical pathway and treatment process.

Recruitment of clinical referral patients will provide genuine, real-world data on patients experiencing mild to moderately severe hearing loss,^1^ allowing the probability of bias in participant selection to be low. The study setting (RCT) and its notably large size (up to 200) are the strengths of this trial, as no previous RCTs of this kind have been conducted before.^6^ The primary limitations of the study are related to the pragmatic design of the trial and its logistical requirements. In addition, the study sample is restricted to individuals who are able to access services at KUH, which may limit the generalisability of the results. In particular, because the trial is embedded in a part of real clinical work, masking will inevitably be affected by this. The variability in the control arm is acknowledged; however, this reflects usual clinical practice and is essential for assessing the added value of a structured data-driven rehabilitation approach under real-world conditions. However, to mitigate variability, systematic tracking and reporting of key variables in the rehabilitation process of both study arms will be conducted. Another limitation is the relatively short follow-up time (short term, 12 months; longer term, 24 months; extended follow-up) for a reliable assessment of cognitive change. However, we plan to conduct a longer follow-up period (10 years) after the intervention.
